## Abstract

**Background:**

Response to neoadjuvant chemoradiotherapy (CRT) of rectal cancer is variable. Accurate imaging for prediction and early assessment of response would enable appropriate stratification of management to reduce treatment morbidity and improve therapeutic outcomes. Use of either diffusion weighted imaging (DWI) or dynamic contrast enhanced (DCE) imaging alone currently lacks sufficient sensitivity and specificity for clinical use to guide individualized treatment in rectal cancer. Multi-parametric MRI and analysis combining DWI and DCE may have potential to improve the accuracy of therapeutic response prediction and assessment.

**Methods:**

This protocol describes a prospective non-interventional single-arm clinical study. Patients with locally advanced rectal cancer undergoing preoperative CRT will prospectively undergo multi-parametric MRI pre-CRT, week 3 CRT, and post-CRT. The protocol consists of DWI using a read-out segmented sequence (RESOLVE), and DCE with pre-contrast T1-weighted (VIBE) scans for T1 calculation, followed by 60 phases at high temporal resolution (TWIST) after gadoversetamide injection. A 3-dimensional voxel-by-voxel technique will be used to produce colour-coded ADC and K^trans^ histograms, and data evaluated in combination using scatter plots. MRI parameters will be correlated with surgical histopathology. Histopathology analysis will be standardized, with chemoradiotherapy response defined according to AJCC 7th Edition Tumour Regression Grade (TRG) criteria. Good response will be defined as TRG 0–1, and poor response will be defined as TRG 2–3.

**Discussion:**

The combination of DWI and DCE can provide information on physiological tumour factors such as cellularity and perfusion that may affect radiotherapy response. If validated, multi-parametric MRI combining DWI and DCE can be used to stratify management in rectal cancer patients. Accurate imaging prediction of patients with a complete response to CRT would enable a ‘watch and wait’ approach, avoiding surgical morbidity in these patients. Consistent and reliable quantitation from standardised protocols is essential in order to establish optimal thresholds of ADC and K^trans^ and permit the role of multi-parametric MRI for early treatment prediction to be properly evaluated.

**Trial registration:**

Australian New Zealand Clinical Trials Registry (ANZCTR) number ACTRN12616001690448 (retrospectively registered 8/12/2016).

## Background

Locally advanced rectal cancer (LARC) requires multi-modality treatment consisting of neoadjuvant chemoradiotherapy (CRT) and standardized surgical technique (total mesorectal excision) [1–3]. Response to neoadjuvant therapy is variable; 15–27% of patients will have a pathologic complete response (pCR) [4], whilst 25–45% will have a poor response with minimal tumour regression [5]. In patients with locally advanced rectal cancer undergoing CRT and surgery, 45% of patients will require permanent colostomy [6]. Accurate imaging for prediction and early assessment of response would enable appropriate stratification of management to reduce treatment morbidity and improve therapeutic outcomes. In patients with a clinical complete response to CRT, substitution of surgery by a ‘watch-and-wait’ approach has emerged as a management option [7–9]. Prediction of poor response could permit trials of dose escalation strategies or curtailment of futile treatment.

Functional magnetic resonance imaging (MRI) has shown promising results for prediction of CRT response in rectal cancer. Diffusion weighted imaging (DWI) has demonstrated greater potential compared with morphologic T2-weighted (T2-w) imaging for the assessment of therapeutic response in rectal cancer patients [10]. However, a systematic review by Joye et al. found that pre-CRT quantitative DWI alone was unable to predict pCR with sensitivity and specificity of 69% and 68%, respectively. Quantitative DWI post-CRT had sensitivity and specificity of 78–80% and 72–78%, respectively, for detecting pCR [11]. Some dynamic contrast enhanced (DCE) MRI studies have shown that higher contrast exchange rate pre-treatment, as indicated by higher K^trans^, is associated with better response to CRT [12, 13]. One study did not find a correlation between pre-treatment K^trans^ and therapeutic response [14]. Use of either DWI or DCE alone currently lacks sufficient accuracy for clinical use to guide individualized treatment in rectal cancer.

Multi-parametric MRI combining DWI and DCE may have potential to improve the accuracy of therapeutic response prediction and assessment. Most published studies describe mean values of a region of interest (ROI) from either DWI or DCE. Single parameter measurements, such as mean apparent diffusion co-efficient (ADC) or K^trans^, do not adequately reflect intra-tumour heterogeneity. A three-dimensional analysis of the tumour volume would provide information on tumour heterogeneity. Development and standardization of multi-parametric imaging protocols is required to provide robust serial imaging datasets and reliable quantitative assessment of treatment response.

### Study hypothesis

Multi-parametric MRI, consisting of DWI and DCE, performed pre-, during- and post- neoadjuvant CRT is predictive of treatment outcome in locally advanced rectal cancer, with histopathology being the standard reference.

## Methods/design

### Study objectives

#### Primary objective

To prospectively evaluate pre-, during- and post-CRT multi-parametric MRI (DWI and DCE) at 3 Tesla for therapeutic response prediction in LARC. MRI biomarkers will be correlated with histopathology tumour regression grade (TRG).

#### Secondary objectives

To prospectively evaluate the role of DCE MRI for therapeutic response prediction and assessment in LARC.To prospectively evaluate the role of DWI MRI (RESOLVE) for therapeutic response prediction and assessment in LARC.To evaluate the different contributions of MRI and PET for therapeutic prediction and assessment in LARC.To correlate MRI biomarkers with 2 year disease-free survival and overall survival.

### Study design

The study design is a prospective, single-arm, cohort study to investigate the value of multi-parametric MRI (combining DWI and DCE) in the prediction and assessment of CRT response. Patients will receive standard treatment for their malignancy. This study does not involve a treatment intervention.

### Study schematic

All patients will receive standard treatment consisting of neoadjuvant CRT followed by surgery, and have MRI and PET performed at three time-points (Fig. 1); pre-CRT, during-CRT (week 3 of CRT), and post-CRT (within 1 week prior to surgery).

**Fig. 1 Fig1:**
[figure not shown]
Study schematic

### Patient selection

#### Inclusion criteria

Age greater than 18Stage II or III rectal adenocarcinoma, defined as T3 - T4 and/or node positive disease (N1–2), without distant metastatic disease (M0)No evidence of metastatic disease on computed tomography (CT) chest/abdomen/pelvisUndergoing treatment regimen consisting of neoadjuvant CRT (Radiotherapy 50.4Gy in 28 fractions delivered using 3D–conformal or VMAT technique concurrent with infusional 5-fluorouracil or oral capecitabine) followed by primary surgery.

#### Exclusion criteria

Other malignancyActive inflammatory bowel diseaseContraindication to MRI:○ Implanted ferromagnetic metal eg. Intraocular metal○ Pacemaker/Implantable defibrillator○ Extreme claustrophobia

#### Treatment

Patients are to undergo standard treatment, consisting of neo-adjuvant long course CRT (as detailed above) followed by surgery, as recommended by treating team. There will be no change to the patient’s treatment from participating in this study.

#### Imaging study procedures

##### Timing of multi-parametric MRI and PET

Pre-CRT: week −2 to 0During-CRT: Week 3 of CRT (early as possible during week 3)Post-CRT: Post completion of CRT, within 1 week prior to surgery

### MRI technique

All MRI scans will be acquired on the 3 Tesla Siemens Skyra (Magnetom, Erlangen, Germany) dedicated MRI-Simulator within the Radiation Oncology department. A 32-channel spine coil integrated in the patient table will be used in combination with an 18-channel phase array surface coil strapped firmly around the pelvis. Butylscopolamine (Buscopan) 20 mg will be administered intravenously prior to acquisition of functional sequences (DWI and DCE) to reduce rectal motion.

#### MRI safety screening

All patients will undergo MRI safety screening.

Screening of suitability for gadolinium-based MRI contrastRequire documentation of normal renal function within three months (eGFR > = 60 ml/min/1.73 m2Contra-indications to use of gadolinium-based MRI contrast/DCE:Renal impairment eGFR <60 ml/min/1.73 m2Acute kidney injuryPrevious allergic reaction to gadolinium-based MRI contrast.

#### MRI sequences

##### T2-weighted turbo spin echo images

- Acquired in 3 planes with 2 mm slice thickness and bandwidth 440 Hz/Px in 1 concatenation: (i) sagittal, (ii) axial oblique, angulated perpendicular to the long tumour axis, and (iii) axial. A T2-w HASTE sequence is additionally acquired in the coronal plane.

##### Diffusion weighted imaging (DWI)

Readout segmented diffusion technique (RESOLVE)Axial orthogonal plane with b-values 50 and 800 s/mm^2^, and 1 & 3 signal averages respectively.ADC maps and calculated b = 1400 mm/s^2^ images produced as part of protocol.In-plane resolution of 1.1 × 1.1 mm and 4 mm slice thickness.

##### Dynamic contrast enhanced (DCE) imaging

Pre-contrast T1-weighted VIBE scans with TR 4.09 ms, TE 1.35 ms, and flip angles 2° and 15° to calculate native T1.DCE acquired with time-resolved angiography with stochastic trajectories (TWIST) technique acquired over 60 phases, with a temporal resolution of 5.28 s, bandwidth 440 Hz/Px, TR 3.67 ms and TE 1.48 ms. Gadoversetamide (Optimark) 0.1 mM/kg injected after 3 phases acquired.

### PET/CT technique

^18^F–FDG PET/CT will be acquired on the GE Discovery-710 PET-CT. Patients need to fast for at least 4 h prior to 4.29 ± 0.34 (mean ± SD) MBq/kg ^18^F -FDG injection and have blood glucose levels <10 mmol/L. All PET scans will be acquired in three-dimensional mode from the mid-brain to proximal femora with an acquisition time of 1.5–2.5 min per bed position, after an ^18^F–FDG uptake time of 60 min. PET data will be reconstructed into a 256 × 256 matrix size with slice thickness of 3.3 mm using GE VUE Point FX (Time of Flight) algorithm. All PET/CT scans will be evaluated on the Advantage Workstation (GE Healthcare) using the AW VolumeShare 5 software and PET-VCAR (Volume Computer-Assisted Reading) protocol.

### Clinical assessment and acute toxicity grading

Radiation Oncology clinical assessments and formal acute toxicity scoring will be performed at the following time points:Pre-CRT: Baseline assessment prior to commencement of treatmentDuring-CRT: Weekly during radiotherapy treatment reviewsPost-CRT: At 2 weeks post-completion of CRT, and within 1 week prior to surgery (ideally at time of post-CRT MRI).
Acute toxicity will be scored according to the ‘Common Terminology Criteria for Adverse Events (CTCAE) Version 4.0.

### Histopathology and tumour regression grade criteria

Histopathological assessment will be undertaken by a dedicated pathology team, with all reporting/TRG assessment by pathologists with sub-specialisation in gastrointestinal pathology. For the study it is a requirement that the whole of the original tumour site should be embedded for microscopic assessment.

MRI will be correlated with histopathological TRG using the modified classification of Ryan et al. [15] set out in the AJCC Cancer Staging Manual, 7th Edition as follows:

*TRG 0 (complete response)* – no viable cancer cells.

*TRG 1 (moderate response)* – single cells or small groups of cancer cells.

*TRG 2 (minimal response)* – residual cancer outgrown by fibrosis.

*TRG 3 (poor response)* – minimal or no tumour kill; extensive residual cancer.

Patients with TRG 0–1 will be categorized as ‘good responders’ and those with TRG 2–3 categorized as ‘poor responders’ to CRT.

### Multi-parametric imaging analysis

A Radiation Oncologist with sub-specialization in gastrointestinal malignancies and a Radiologist with sub-specialization in pelvic MRI will perform all segmentations. K^trans^ maps will be produced by first pre-selecting an appropriate arterial input function, scaled by dose, based on chi-squared goodness of fit, and using a two-compartment Tofts model [16]. ADC and K^trans^ parameter maps will be exported in DICOM format and registered to T2-w axial images.

The region of interest for analysis will be defined on the entire hyper-intense primary tumour on the b-value 1400 mm/s s^2^ images. A voxel-by-voxel technique will be used to produce colour-coded maps and histograms of ADC and K^trans^, and combined scatterplots for each time-point.

### Statistical considerations

A target of 35 patients will be recruited; this is estimated to take 24 months. For estimated pCR rate of 25%, 35 patients will provide 80% power to detect an AUC ≥ 80%. Poor responders rate is estimated to be in the range of 25–45% [5]. For estimated poor responder rate of 25%, 35 patients will provide 80% power to detect an AUC ≥ 80%. For estimated poor responder rate of 45%, 35 patients will provide 80% power to detect an AUC ≥ 76%.

Univariate analysis will be performed to investigate the association between each MRI parameter and tumour regression grade (AJCC 7th edition). Each MRI parameter will be correlated with pathologic complete responders (pCR - TRG 0) using a 2 × 2 Table. A similar analysis will be performed for good responders (TRG0–1) vs. poor responders (TRG 2–3). Receiver operator characteristics curves will be used to obtain an optimal threshold for each MRI parameter (ADC and K^trans^).

Multivariate analysis will be performed to investigate the association between multi-parametric MRI and tumour regression grade. The multi-parametric MRI parameters that will be used for multivariate analysis are ADC and K^trans^.

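### The 80% power is stated for an AUC, but the only univariate analysis named is a 2 × 2 table at an ROC-derived threshold, which does not carry that power at a 5% error rate

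*Protocol article*

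**What the plan says.** All the relevant text is in the protocol article, Statistical considerations.

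- Size: "A target of 35 patients will be recruited; this is estimated to take 24 months".
- Power for complete response: "For estimated pCR rate of 25%, 35 patients will provide 80% power to detect an AUC ≥ 80" per cent.
- Power for poor response at the low rate: "For estimated poor responder rate of 25%, 35 patients will provide 80% power to detect an AUC ≥ 80" per cent.
- Power for poor response at the high rate: "For estimated poor responder rate of 45%, 35 patients will provide 80% power to detect an AUC ≥ 76" per cent.
- Univariate analysis: "Each MRI parameter will be correlated with pathologic complete responders (pCR - TRG 0) using a 2 × 2 Table", and then "A similar analysis will be performed for good responders (TRG0–1) vs. poor responders (TRG 2–3").
- Role of the ROC curve: "Receiver operator characteristics curves will be used to obtain an optimal threshold for each MRI parameter", the parameters being ADC and Ktrans.

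The section also announces, in general terms, a univariate analysis of each parameter against regression grade and a multivariate analysis using ADC and Ktrans. It states no alpha, no null AUC, no cut-off fixed in advance and no test for the 2 × 2 table.

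**The concern.** An AUC measures how well the full range of a continuous marker separates two groups. A 2 × 2 table keeps only whether each patient lies above or below one cut-off. If power is calculated for the first and the association is judged by the second, the power figure describes an analysis that the text does not contain.

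The source of the cut-off adds a second problem. If it is chosen to separate the groups best in the same patients, an ordinary test on the resulting table takes no account of the search, and associations appear too often. The Discussion presents optimal thresholds for ADC and Ktrans as the goal and, if they are validated, use of the imaging to stratify management. Optimistic thresholds and associations would feed directly into that.

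**Working it through.** **Inputs.** From Statistical considerations: 35 patients, rates of 25% and 45%, AUCs of 0.80 and 0.76, power 80%. Group sizes: 0.25 × 35 = 8.75, taken as 9 versus 26; 0.45 × 35 = 15.75, taken as 16 versus 19. Assumed, because not stated: alpha 0.05 two-sided, null AUC 0.50, all 35 evaluable, and normally distributed markers with equal variance in both groups (binormal).

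**Step 1: reproduce the plan's figure.** With the Obuchowski binormal variance, a = 1.414 × Φ⁻¹(AUC) and k = n0/n1:

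Var(AUC) = 0.0099 × exp(−a²/2) × [(5a² + 8) + (a² + 8)/k] / n1

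Power = Φ[(AUC − 0.5 − 1.96 × SE0) / SE_A]

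SE0 is the standard error at AUC 0.50 and SE_A the one at the target AUC.

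- AUC 0.80, 9 versus 26: SE0 = 0.1088, SE_A = 0.0997. (0.30 − 0.2132)/0.0997 = 0.87, so power is 80.8% (80.0% with 8.75 and 26.25).
- AUC 0.76, 16 versus 19: SE0 = 0.0955, SE_A = 0.0879. (0.26 − 0.1872)/0.0879 = 0.83, so power is 79.6%.

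The Hanley-McNeil variance gives 79.2% and 78.2%, and a simulated exact Mann-Whitney test gives 81.8% and 78.3%. One-sided 5% gives about 88% and does not fit. The stated 80% is thus the power of a two-sided test of a continuous marker.

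**Step 2: a 2 × 2 table at a cut-off fixed in advance.** The separation of the group means is d = √2 × Φ⁻¹(AUC). The best cut-off is d/2, where sensitivity = specificity = Φ(d/2).

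- AUC 0.80: d = 1.190, sensitivity = specificity = 0.724.
- AUC 0.76: d = 0.999, sensitivity = specificity = 0.691.

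Power follows by enumerating all tables with these binomial probabilities (first three rows of results below).

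**Step 3: a 2 × 2 table at a cut-off chosen on the same data.** In 20,000 simulated trials per setting, the cut-off maximised the absolute Youden index and Fisher's test was applied to the resulting table. The same index was then calibrated to 5% under the null.

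| Analysis | AUC 0.80, 9 v 26 | AUC 0.76, 16 v 19 |
|---|---|---|
| AUC test, continuous marker: power | 80.8% | 79.6% |
| Fixed ideal cut-off, Fisher: power | 60.1% | 60.6% |
| Fixed ideal cut-off, chi-square: power | 68.8% | 61.8% |
| Fixed ideal cut-off, Yates: power | 55.2% | 48.4% |
| Data-chosen cut-off, ordinary Fisher: type I error | 21.5% | 26.2% |
| Data-chosen cut-off, ordinary chi-square: type I error | 33.1% | 31.6% |
| Data-chosen cut-off, ordinary Fisher: rejection at target AUC | 91.8% | 91.5% |
| Data-chosen cut-off, calibrated to 5%: power | about 75% | about 70% |

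A separate simulation of the same settings gave 21% and 27% for the Fisher type I error, and 72% and 70% for calibrated power.

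The type I errors let the data choose the direction of the association. If the direction were fixed beforehand, symmetry roughly halves them, to about 21.5/2 = 11% and 26.2/2 = 13%. The nominal share of a two-sided 5% test in that direction is 2.5%, so the relative inflation is the same.

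**The case against.** The strongest reply is that the text never calls the 2 × 2 table a hypothesis test. It attaches no p-value, alpha or named test to it. In a diagnostic study such a table is the usual source of sensitivity and specificity, which are the measures the Background uses to judge DWI. A general sentence announces a univariate analysis that could include a rank test, and an ROC curve yields an AUC in any case. A journal article may also leave the exact test to a fuller plan that is not shown.

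Much of this stands. The inflated error arises only if someone tests the table at the optimised threshold, and a purely descriptive table would be unobjectionable. The Discussion also makes clinical use conditional on validation. What does not go away is that the table is the one stated means of relating each parameter to response, the ROC curve has the single stated task of finding a threshold, and no AUC test appears. This is a mismatch between two things the section does state, not a complaint about missing detail.

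Two stronger readings should be resisted.

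- A reader might infer that the planned analysis has only about 60% power. That figure needs Fisher's test at an ideal cut-off fixed in advance, and the document states neither. It takes its threshold from ROC curves, where the main fault is false positives, and calibrated power is about 70–75%.
- A reader might infer that 35 patients are too few. The stated power reproduces for an AUC test, so the documents do not support that inference.

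**Conclusion.** The point holds as a mismatch of moderate weight. The power figures belong to a two-sided 5% test of the AUC against 0.50, whereas the named univariate analysis is a 2 × 2 table at an ROC-derived threshold. Neither version of that table delivers 80% power at 5% error. With a same-data threshold, the choice is between an ordinary Fisher test with roughly four to five times the nominal error (21.5/5 = 4.3; 26.2/5 = 5.2) and a calibrated test 5 to 10 points short of 80%. With an ideal threshold fixed in advance, the shortfall is about 11 to 20 points by chi-square or Fisher, and more with Yates.

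These sizes rest on the equal-variance binormal model, the inferred alpha and null, full evaluability, and the reading that the threshold comes from the study's own patients, which the text implies but does not say.

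**What to change.** In Statistical considerations, name the AUC against 0.50 (Mann-Whitney or DeLong) as the powered univariate analysis, with ADC and Ktrans kept continuous, and state the two-sided 5% level and the null value on which the power rests.

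Keep the 2 × 2 tables as description: sensitivity, specificity and predictive values with confidence intervals at the ROC threshold, labelled as derived on the same data and likely to be optimistic, without a p-value.

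If the investigators want the 2 × 2 table to remain the test, the cut-off should be fixed in advance and the power recalculated for the particular test chosen. A single replacement figure should not be written in before that choice is made.

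The preferred change costs a few sentences and no patients, scans or data. The one loss is that the 2 × 2 results no longer have inferential standing.

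### ROC-optimal cut-offs for ADC and Ktrans, cross-tabulated in the same 35 patients, would overstate accuracy and inflate the error rate of a 2 × 2 test

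*Protocol article*

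**What the plan says.** All of this is in the protocol article. Under Statistical considerations:

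- Cohort: "A target of 35 patients will be recruited". Study design describes a single-arm cohort, and no second or hold-out group appears anywhere.
- Tables: "Each MRI parameter will be correlated with pathologic complete responders (pCR - TRG 0) using a 2 × 2 Table". A matching analysis is planned for TRG 0–1 against TRG 2–3.
- Cut-offs: "Receiver operator characteristics curves will be used to obtain an optimal threshold for each MRI parameter", the parameters being ADC and Ktrans. No numerical cut-off is given in advance, and the criterion for the optimum is not named.
- Sample size: justified on the AUC, for example "For estimated pCR rate of 25%, 35 patients will provide 80% power to detect an AUC ≥ 80" (per cent).

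The Discussion of the abstract shows that thresholds are an intended product: "Consistent and reliable quantitation from standardised protocols is essential in order to establish optimal thresholds of ADC" (and of Ktrans). There and in the main Discussion, clinical use is made conditional on validation.

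**The concern.** ADC and Ktrans are continuous, so neither can enter a 2 × 2 table without a cut-off. The ROC-derived threshold is the only source of one that the protocol describes, and the 35 patients are the only data. Followed as written, the plan picks the cut-off that best separates these patients and then tabulates the same patients at it.

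A cut-off chosen this way partly fits noise. The sensitivity and specificity read from the table are then too high on average, and a test on the table no longer holds its nominal level, because the largest of many possible contrasts has been selected. With about 9 patients in the smaller group, neither effect is negligible.

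The Background judges pre-CRT DWI inadequate at 69% sensitivity and 68% specificity. An uncorrected table could make a marker that is truly worse than this look better.

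**Working it through.** **Inputs.** From Statistical considerations: n = 35; pCR rate 25% (0.25 × 35 = 8.75, about 9 against 26) with AUC 0.80; poor-responder rate 25% with AUC 0.80 (same split) or 45% with AUC 0.76 (0.45 × 35 = 15.75, about 16 against 19). Assumed, because the article does not state them: two-sided alpha 0.05, an equal-variance binormal marker, the Youden criterion, and one parameter at one time-point.

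**Step 1: the plan's own power.** Hanley–McNeil variance, with n1 and n0 the group sizes:

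Var(A) = [A(1−A) + (n1−1)(A/(2−A) − A²) + (n0−1)(2A²/(1+A) − A²)] / (n1·n0)

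Power = Φ{[(A − 0.5) − 1.96·SE(0.5)] / SE(A)}

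- 9/26, A = 0.80: SE(0.5) = √(3.000/234) = 0.1132; SE(0.80) = √(2.151/234) = 0.0959. Power = Φ[(0.300 − 0.222)/0.0959] = Φ(0.81) = 79.2%.
- 16/19, A = 0.76: SE(0.5) = √(3.000/304) = 0.0993; SE(0.76) = √(2.130/304) = 0.0837. Power = Φ[(0.260 − 0.195)/0.0837] = Φ(0.78) = 78.2%.

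The Obuchowski binormal variance gives 80.8% and 79.6%. The stated 80% reproduces to within 2 points. It concerns the AUC and says nothing about accuracy at a chosen cut-off.

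**Step 2: optimism of the chosen cut-off.** Marker values are N(d, 1) in one group and N(0, 1) in the other, with d = √2·Φ⁻¹(AUC). In each of 20,000 simulated trials, c is the cut-off that maximises sensitivity + specificity in the sample. Its true sensitivity is 1 − Φ(c − d) and its true specificity is Φ(c). Means:

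| Split | AUC | Apparent sens/spec | True sens/spec at chosen cut-off | Overstatement (points) |
|---|---|---|---|---|
| 9/26 | 0.70 | 74.3% / 70.0% | 60.2% / 65.1% | 14.1 / 4.9 |
| 9/26 | 0.76 | 77.8% / 74.4% | 64.4% / 69.9% | 13.4 / 4.5 |
| 9/26 | 0.80 | 80.6% / 77.4% | 67.7% / 73.1% | 12.9 / 4.3 |
| 16/19 | 0.70 | 71.7% / 70.3% | 62.8% / 62.8% | 8.9 / 7.5 |
| 16/19 | 0.76 | 76.1% / 74.1% | 67.8% / 67.0% | 8.3 / 7.1 |
| 16/19 | 0.80 | 78.8% / 77.2% | 71.0% / 70.5% | 7.8 / 6.7 |

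A repeat run at 9/26, AUC 0.70 gave 74%/70% against 59%/65%, which is 15 points on sensitivity.

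**Step 3: level of a test at that cut-off.** AUC 0.50, nominal 5%:

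| Test on the 2 × 2 table | 9/26 | 16/19 |
|---|---|---|
| Fisher, cut-off fixed beforehand | 3.2% | 4.1% |
| Fisher, optimised cut-off, direction fixed | 10.6% | 13.4% |
| Fisher, optimised cut-off, direction free | 20.6% | 25.4% |
| Chi-square without correction, direction free | 33.1% | 32.2% |

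Across repeat runs, Fisher's test ranged over about 11–14% with direction fixed and 20–27% with it free.

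**Step 4: against the cited 69%/68%.** At 9/26 and AUC 0.70, the apparent 74%/70% exceeds it on both measures while the true 60%/65% falls short on both. At AUC 0.50 with direction free, the apparent means are about 68%/62%, below it on both, and only about 3% of simulated trials reach 69%/68% on both.

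**Step 5: what resampling recovers.** The cut-off was re-selected in each of 100 bootstrap samples (1,000 simulated trials). At 9/26, AUC 0.80, 81%/77% falls to 74%/74%, against a truth of 68%/73%. At 16/19, AUC 0.76, 76%/75% falls to 70%/71%, against 67%/68%. In the first case 7.6 of the 13.3 points of optimism in sensitivity are removed (81.3 − 73.7, and 81.3 − 68.0).

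**The case against.** The strongest reply is that much of this is inferred. The section does not say that the 2 × 2 table uses the ROC cut-off, does not name sensitivity, specificity or a particular test, and says nothing either way about resampling. A condensed article may leave resampling to a full protocol or SAP. That stands as a limit: the absence of a validation paragraph is not the finding. The finding rests on what the section does fix, namely data-derived cut-offs and 2 × 2 tables for continuous parameters in one cohort.

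It can also be said that the sample size rests on the AUC, that treatment does not change within the study, and that clinical use is conditional on validation. All true. But a remark about later validation does not correct the accuracy that this study itself would report.

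A reader might infer that a worthless marker would look as good as the cited DWI results. The numbers do not support that: its average apparent accuracy lies below the pre-CRT pair (69%/68%) and further below the post-CRT ranges (78–80%/72–78%). A reader might also quote only the free-direction error rates. The Background gives a prior direction for pre-treatment Ktrans from some studies (another found no correlation), so the fixed-direction figures belong beside them.

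**Conclusion.** The point holds for the threshold-based results. On the natural reading of Statistical considerations, sensitivity would be overstated by about 8 to 15 points and specificity by about 4 to 8 at true AUCs of 0.70 to 0.80. A Fisher test at the optimised cut-off would have a type I error of about 11–14% (direction fixed) to 20–27% (direction free). The practical risk is that a weakly to moderately informative marker, with AUC near 0.70, appears on average to beat the pre-CRT DWI figures although it is truly below them.

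The single-parameter AUC and the power statement are not in question. The sizes depend on the binormal and Youden assumptions and on one parameter at one time-point. Choosing among two parameters, three time-points and two response splits would add further selection, which is not counted here.

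**What to change.** Amend Statistical considerations, or the SAP if there is one, before the outcome data are analysed:

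1. Base inference for each parameter on the threshold-free AUC, tested by Mann–Whitney, and not on a 2 × 2 test at the optimised cut-off.
2. Name the criterion for the optimal cut-off. Repeat the whole selection within each bootstrap resample or cross-validation fold, and report optimism-corrected sensitivity and specificity with confidence intervals beside the apparent values.
3. State that the correction is only partial at this sample size, so the corrected figures are not presented as unbiased.
4. Label the thresholds exploratory pending evaluation in an independent cohort.

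This needs no extra patients or scans. It costs a paragraph of text and a little more analysis, and the reported accuracy will look less favourable.
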